#### 5.2 Research Design and Outline

##### 5.2.1 Research Design

1. Nature of the study: exploratory
2. Randomization: single-arm
3. Blinding: open-label
4. Control: none
5. Allocation: none

##### 5.2.2 Research Outline

Remote monitoring via the CareLink system (Medtronic) will be conducted every 6 months for 3 years post-implantation. Outpatient follow-up visits every 1–3 months will continue as before.

#### 5.3 Subject Registration and Allocation Method

1. **Registration Method**
   The principal or sub-investigator will confirm that the patient meets all inclusion and no exclusion criteria after obtaining written informed consent. Then, those engaged in this clinical research will enter the patient data into the EDC system to register the subject.
2. **Allocation Method**
   There is no group allocation in this single-arm study.

#### 5.4 Overview of the Investigational Device

We will use the following devices. The “Medtronic Reveal LINQ Mobile Manager” and “Medtronic 24967 Patient Connector” are already available at the study institution.

- **General Name**: Implantable ECG Data Recorder
  **Product Name**: Medtronic LINQ II
  **Class**: Highly controlled medical device (Class IV)
  **Intended Use/Effect**: For patients with unexplained syncope/palpitations, or for monitoring AF in cryptogenic stroke patients, by continuous subcutaneous ECG recording.
  **Approval Number**: 30300BZX00278000 (October 2021)
  **Manufacturer**: Medtronic Japan
- **General Name**: Program for management of implantable active devices
  **Product Name**: Medtronic Reveal LINQ Mobile Manager
  **Class**: Class III
  **Approval Number**: 22800BZX00305000 (August 2016)
  **Manufacturer**: Medtronic Japan
- **General Name**: Programmer for implantable active devices
  **Product Name**: Medtronic 24967 Patient Connector
  **Class**: Class III
  **Approval Number**: 30100BZX00034000 (June 2019)
  **Manufacturer**: Medtronic Japan

Because AF monitoring is not an approved indication in Japan (currently limited to unexplained syncope and cryptogenic stroke), its use for AF monitoring in HFrEF is off-label domestically, although widely used overseas for AF detection.

**Usage Summary**: LINQ II is a small, lightweight ECG monitoring device (45×8×4.2 mm, 4 g). It is implanted about 8 mm under the skin in the left anterior chest using a specialized kit, and configured for remote monitoring with the dedicated connector/programmer. ECG data are periodically transmitted to the server, allowing the medical staff to review the patient’s ECG as needed.

#### 5.5 Procedures for Managing the Investigational Device

The devices are supplied by Medtronic Japan to the principal investigator and stored at the designated location in TMDU Hospital. Storage conditions and usage deadlines adhere to the package insert. The principal investigator is responsible for device management.

#### 5.6 Planned Participation Period for Subjects

Approximately 3 years after providing consent. If an adverse event is suspected to be related to the study beyond that period, follow-up will continue until it is deemed resolved.

#### 5.7 Discontinuation Criteria for the Overall Study

The principal investigator will consider whether to continue the study if any of the following occurs:

- Discovery of critical information impacting device quality, performance, or safety
- Difficulty in enrolling enough subjects
- Early achievement of study objectives
- Instructions to modify the protocol from the Certified Review Board that cannot be accepted
- The CRB discontinues the study
- Serious or ongoing violations of the Clinical Trials Act, its enforcement regulations, or this protocol

### **6. Criteria for Selection and Exclusion of Study Subjects**

#### 6.1 Study Subjects (Target Disease)

Patients with HFrEF who are not diagnosed with AF

#### 6.2 Inclusion Criteria

All conditions must be met:

1. HFrEF (LVEF ≤40%)
2. Receiving appropriate pharmacotherapy for HFrEF; currently attending outpatient or able to do so
3. CHADS2 score ≥1
4. Age ≥20 at time of consent
5. Written informed consent

#### 6.3 Exclusion Criteria

Any of the following:

1. Already implanted with a CIED capable of detecting supraventricular arrhythmias
2. Diagnosed with AF at time of consent
3. Life expectancy <1 year
4. Immunocompromised
5. Active infection
6. Subcutaneous tissue too thin at implant site for safe ILR placement
7. Otherwise deemed inappropriate

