**Exclusion Criteria**
Any of the following:

1. Patients who already have an implanted cardiovascular electronic device (CIED) capable of detecting supraventricular arrhythmias (i.e., a permanent pacemaker, ICD, or ILR)
2. Patients diagnosed with AF at the time of consent
3. Patients whose life expectancy is considered to be within 1 year
4. Patients in an immunocompromised state
5. Patients with an active infection
6. Patients whose subcutaneous tissue is too thin at the implantation site, making safe ILR implantation difficult
7. Any patient deemed inappropriate for this study by the principal or sub-investigator

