For HFrEF patients (who are at high risk of developing AF and other arrhythmias), continuous ECG monitoring by ILR may facilitate the earlier detection of arrhythmias and earlier therapeutic intervention, potentially improving mortality.

Since there are no published data on ILR-based continuous ECG monitoring in the target population of this study (patients with HFrEF), the exact incidence of newly identified arrhythmias remains unclear. This study is exploratory, enrolling up to 35 patients who are likely eligible for ILR implantation over 2 years, to examine the exploratory utility of ILR for HFrEF. Patients may benefit from earlier detection and intervention for arrhythmias. Potential disadvantages include skin-related complications (infection, erosion, bleeding, etc.) at the implantation site. Early overseas reports in patients receiving ILRs for unexplained syncope, unexplained stroke, or AF monitoring indicated a complication rate of about 1.5%, with about half resolving conservatively and the other half requiring device explant. We will follow subjects for one year (the main analysis time point) and continue observation for up to three years, matching the battery life of the device. Should promising results be obtained, we will consider, in collaboration with the manufacturer, the possibility of conducting a subsequent clinical trial aimed at expanding indications to use ILRs for HF patients.

1. Okura Y, et al. Impending epidemic: future projection of heart failure in Japan to the year 2055. Circ J 2008; 72: 489-491.
2. Guidelines for Diagnosis and Treatment of Acute and Chronic Heart Failure （JCS 2017/JHFS 2017）
3. JCS/JHRS 2019 Guideline on Non-Pharmacotherapy of Cardiac Arrhythmias
4. Aguilar M, et al. Influence of Monitoring Strategy on Assessment of Ablation Success and Postablation Atrial Fibrillation Burden Assessment: Implications for Practice and Clinical Trial Design. Circulation. 2022;145:21-30.
5. Sanna T, et al. Cryptogenic stroke and underlying atrial fibrillation. N Engl J Med. 2014;370:2478-86.
6. Mittal S, et al. Safety Profile of a Miniaturized Insertable Cardiac Monitor: Results from Two Prospective Trials. Pacing Clin Electrophysiol. 2015;38:1464-9.

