### **5. Details of the Clinical Research**

#### 5.1 Primary and Secondary Endpoints

#### (See “8. Evaluation of Efficacy” for details.) The primary analysis will use data at 1 year post-implantation; after all patients have completed the 3-year follow-up, a final analysis will be performed.

- **Primary Endpoint**
  Proportion of patients in whom AF or non-sustained or sustained VT is detected

Definition: Among the analysis population, the percentage of patients with any of:

- - AF lasting ≥6 minutes
  - Non-sustained VT: heart rate >150 bpm, ≥16 consecutive beats, ≤30 s
  - Sustained VT: heart rate >150 bpm, lasting ≥30 s

Rationale: These arrhythmias would clinically warrant consideration of intervention (pharmacological, ablation, or device-based).

- **Secondary Endpoints**
  - Proportion of patients with pauses ≥4.5 seconds
  - Proportion of patients with bradycardia <30 bpm
  - Proportion of patients with high-grade AV block
  - Proportion of patients receiving permanent pacemakers, ICDs, catheter ablation, or antiarrhythmic drug therapy
  - All-cause mortality
  - Cardiovascular mortality
  - Proportion of patients requiring hospitalization for cardiovascular disease or heart failure
  - Proportion of patients experiencing stroke

Rationale:

- - (1)–(3): They may require consideration of therapeutic intervention.
  - (4): To evaluate the effect of continuous ECG monitoring by ILR on treatment decisions.
  - (5)–(8): To evaluate the relationship between ILR findings and clinical outcomes.
- **Safety Evaluation Items**
  - Incidence of adverse events related to ILR implantation
  - Incidence of malfunctions

(Rationale: General safety assessment items.)

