### **7. Treatment for Study Subjects**

#### 7.1 Implementation Procedures for the Study Treatment

##### 7.1.1 From Informed Consent to Registration, Evaluations at Registration

- The principal/sub-investigator will confirm eligibility and explain the study, obtaining written informed consent.
- After consent, baseline data and relevant tests will be done (see “7.2”).
- Registration is completed by entering subject data into the EDC.
- If required tests performed within 30 days before registration are available, those can be used.
- Baseline ECG: the heart rhythm is confirmed on a monitor ECG at ILR implantation.

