##### 7.2.2 Observation/Examination Items

1. **Informed Consent**
   Date of written informed consent
2. **Subject Background**
   - **Basic info**: DOB, age, sex, height, weight, BMI
   - **Comorbidities**: HF, hypertension, diabetes, stroke/TIA (for CHADS2), vascular disease (for CHA2DS2-VASc)
   - **Dialysis**: presence or absence
   - **Past cardiac surgery**: type, date
   - **Hospitalization history for HF**: presence, number of admissions, most recent admission date
   - **Current medications**: antiplatelet/anticoagulants, diuretics, beta-blockers, RAA inhibitors, MRAs, SGLT2 inhibitors, other HF therapies, antiarrhythmics
3. **Pre-implantation (Registration) Tests**
   - **Echocardiogram**: LAD, LVDd, LVDs, LVEF, IVS, LVPW, etc.
   - **Blood test**: BNP
   - **ECG**: 12-lead ECG to confirm rhythm (sinus, AF/flutter, paced, etc.)
   - **Chest X-ray**: cardio-thoracic ratio (CTR)
4. **At Implantation**
   - **ECG**: Monitor ECG (or 12-lead if possible) to confirm rhythm
5. **ILR Remote Monitoring**
   - Date of evaluation, evaluator
   - **AF ≥6 minutes**: presence/absence, date/time, number of events, total duration, etc.
   - **Non-sustained VT** (HR >150, ≥16 beats, ≤30 s)
   - **Sustained VT** (HR >150, ≥30 s)
   - **Pauses ≥4.5 s**
   - **Bradycardia <30 bpm**
   - **High-grade AV block**
6. **Clinical Course**
   - Mortality (date, CV or non-CV, details)
   - CV or HF hospitalizations (date, details)
   - Stroke (date, details)
   - Implantation of a permanent pacemaker, ICD therapy, catheter ablation, AAD therapy (dates, details)
7. **Adverse Events**
   - Onset date, resolution date, severity (Grade), treatment, outcome, seriousness, relationship to ILR, whether ILR explanted, etc.
8. **Device Malfunctions**
   - Malfunction name, onset/end date, presence of adverse event, whether ILR explanted, etc.

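### Prior ventricular tachycardia is neither excluded nor recorded at baseline, so the primary proportion mixes recurrence of known arrhythmia with new detection

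*Protocol*

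**What the plan says.** **Eligibility.** Section 6.3 lists seven exclusions. The only one that names an arrhythmia is "Diagnosed with AF at time of consent"; the overview in section 1 has the same time anchor ("Patients diagnosed with AF at the time of consent"). VT is not named. A discretionary item remains: "Otherwise deemed inappropriate". Patients who already carry a pacemaker, ICD or loop recorder are excluded.

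**Endpoint.** The primary endpoint in section 5.1 is "Proportion of patients in whom AF or non-sustained or sustained VT is detected". AF must last at least 6 minutes. A ventricular run must exceed 150 bpm, and a non-sustained one must reach 16 beats. Nothing requires the arrhythmia to be new to the patient. The full analysis set in section 10.1 keeps every enrolled subject who received a device.

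**Baseline data.** The comorbidities in section 7.2.2 are "HF, hypertension, diabetes, stroke/TIA (for CHADS2), vascular disease (for CHA2DS2-VASc"). Dialysis, cardiac surgery, heart-failure admissions and current drugs (antiarrhythmics among them) are also collected. A history of VT is not listed. The registration ECG is "12-lead ECG to confirm rhythm (sinus, AF/flutter, paced, etc".).

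**Timing.** Section 7.1.1 states: "After consent, baseline data and relevant tests will be done". The rhythm is checked again at implantation, which may be up to 30 days after registration (section 7.1.2).

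**Stated interest.** Section 3 gives the gap in knowledge: "the exact incidence of newly identified arrhythmias remains unclear".

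**The concern.** Two of the three components of the primary endpoint are ventricular. Excluding known AF lets an AF detection be read as new, but there is no matching step for VT. Section 3 itself describes ventricular arrhythmias as common in this disease, so patients with a documented run and no device are foreseeable at enrolment. When such a patient has a qualifying run on the recorder, the primary proportion counts a recurrence in the same way as a new detection.

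This matters because the study has no control group. The one proportion is the main evidence on yield, and section 3 says promising results could lead to a trial aimed at wider indications. A reader will tend to take the figure as what the device finds that routine care had not.

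**Working it through.** **Step 1: trace a patient with known VT and no device.**
- Section 6.3: no named exclusion applies, so entry is barred only at the investigator's discretion.
- Section 7.2.2: the history has no listed field. Antiarrhythmic use is recorded but does not identify prior non-sustained VT.
- Section 5.1: the patient counts once the recorder stores a run above 150 bpm of at least 16 beats. A shorter recurrence does not count.
- Section 10.1: no analysis-set rule removes or separates the patient.

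**Step 2: trace a patient whose AF is first seen after consent.**
- Section 6.3 dates the exclusion to consent. The registration ECG may come later, and the implant check always does.
- AF/flutter is a recordable result, but no eligibility, discontinuation (section 7.6) or analysis-set rule names it.
- On the other side, section 5.3 has eligibility confirmed after consent, section 6.1 defines the population as not diagnosed with AF, section 7.1.1 allows an ECG from the 30 days before registration, and the discretionary exclusion is available. Exclusion at registration is therefore likely. AF first seen at implantation, after registration, is the case left without a rule.

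**Step 3: size.** The plan offers no figure to reproduce: section 10.2 gives 35 subjects without an expected rate or precision. The following inputs are assumptions:
- q, the detection rate in patients without prior arrhythmia: 10-30%
- k, the number of patients with prior arrhythmia: 1 to 7 of 35
- r, the chance that the recorder captures a qualifying episode in them: 50-100%

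Observed proportion = ((35 − k)q + kr)/35. Shift from q = k(r − q)/35, which is upward whenever r exceeds q.

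At q = 20%:

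| k | Observed, r = 50% | Observed, r = 100% | Shift (points) |
|---|---|---|---|
| 1 | 20.9% | 22.3% | 0.9 to 2.3 |
| 2 | 21.7% | 24.6% | 1.7 to 4.6 |
| 4 | 23.4% | 29.1% | 3.4 to 9.1 |
| 7 | 26.0% | 36.0% | 6.0 to 16.0 |

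For example, k = 4 and r = 100% gives (31 × 0.20 + 4)/35 = 10.2/35 = 29.1%.

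Over the whole assumed range, the shift runs from 1 × (0.5 − 0.3)/35 = 0.6 points to 7 × (1.0 − 0.1)/35 = 18.0 points.

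The gross weight of one patient is 1/35 = 2.9 points. The net shift is smaller, because a patient without the history would already have had chance q of counting: (1 − 0.20)/35 = 2.3 points.

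For scale, the exact 95% interval for 7/35 is 8.4% to 36.9%.

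**Step 4: the denominator of a newly identified estimate.** With k = 4 and q = 20%, new detections number 31 × 0.20 = 6.2. Over 35 that is 17.7% if the four contribute nothing new; over the 31 without prior arrhythmia it is 20%. The denominator has to be stated.

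**The case against.** The strongest reply is that the endpoint is computed correctly as defined. Section 4 states the purpose as detecting asymptomatic arrhythmias, and the rationale in section 5.1 is that these arrhythmias would prompt consideration of treatment. Neither requires novelty; that interest appears in section 3. This stands, and it is why the all-detections proportion should be kept. It does not remove the ambiguity, because that proportion alone cannot answer the question posed in section 3.

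A second reply is that the shifts at q = 20% all lie within the exact interval for 7/35, in a study labelled exploratory. That is true, but the interval reflects sampling error only and gives no sign of a systematic upward shift.

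Three stronger readings are tempting, and the documents do not support them:
- A reader might infer that AF on a baseline ECG would lead to implantation and a counted detection. The text does not show this: the provisions in step 2 make exclusion at registration likely, and the patient would still need an AF episode of at least 6 minutes on the recorder.
- A reader might infer that the mixing could never be undone. For AF, baseline rhythm is recorded before and at implantation. For VT, medical records are source documents (section 11) and are retained (section 14.2), so chart review at this single centre is possible, although not planned.
- A reader might infer that every patient with known VT counts. Those with an ICD or pacemaker are excluded, and the others need a qualifying run.

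**Conclusion.** The point holds for ventricular arrhythmia. As written, the primary proportion combines recurrence of known VT with new detection, and the listed baseline items do not separate the two. Relative to newly identified arrhythmia, the direction is upward if patients with prior VT are more likely than others to have a qualifying episode, which is the assumption used here. The size cannot be derived from the documents. At an assumed 20% new-detection rate, one such patient moves the estimate by 0.9 to 2.3 points and four by 3.4 to 9.1 points.

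The AF part is a lesser matter of wording: the exclusion is anchored to consent, and the protocol is silent on AF first seen on a later registration or implant ECG.

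The documents do not show that the primary endpoint is invalid or must be replaced.

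**What to change.** 1. Add prior documented VT, sustained or non-sustained, to the subject background in section 7.2.2, with date, source, and rate and run length where known. An analysis plan cannot supply this if the item is not collected.
2. Keep the all-detections primary proportion. Beside it, pre-specify the proportion with a newly identified arrhythmia. A component does not count for a patient in whom an arrhythmia meeting the same endpoint definition was documented before implantation. Matching on the definition keeps a first qualifying run in a patient whose history holds only shorter runs. State the denominator, and show AF and VT separately.
3. Reword exclusion 2, in sections 1 and 6.3, to AF diagnosed at any time up to implantation of the recorder, including on the registration and implant ECGs.

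The cost is one more CRF item, a possibly lower figure for newly identified yield, an occasional late screen failure, and a protocol amendment under section 22.2, with review-board approval and, if the implementation plan changes, ministerial notification and jRCT publication. No extra test is needed.

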### **7. Treatment for Study Subjects**

#### 7.1 Implementation Procedures for the Study Treatment

##### 7.1.1 From Informed Consent to Registration, Evaluations at Registration

- The principal/sub-investigator will confirm eligibility and explain the study, obtaining written informed consent.
- After consent, baseline data and relevant tests will be done (see “7.2”).
- Registration is completed by entering subject data into the EDC.
- If required tests performed within 30 days before registration are available, those can be used.
- Baseline ECG: the heart rhythm is confirmed on a monitor ECG at ILR implantation.

##### 7.1.2 ILR Implantation

- Within 30 days after registration, the ILR is implanted (usually outpatient basis, possibly inpatient if necessary). If it cannot be done within 30 days, protocol treatment is discontinued.
- Implantation steps (outline):
  1. Implant site: 4th intercostal space in the left anterior chest.
  2. Local disinfection with povidone-iodine, local anesthesia, small incision, creation of a subcutaneous pocket (~8 mm depth).
  3. Insert the ILR device using the supplied introducer.
  4. Confirm adequate ECG signal via the programmer (Reveal LINQ Mobile Manager) before closing.
  5. No prophylactic antibiotics are used.
  6. The device is programmed for continuous monitoring (remote monitoring) settings.

##### 7.1.3 Remote Monitoring

- The CareLink system (Medtronic) transmits data from a home-based communicator (“MyCareLink Relay”) to a dedicated server. Physicians can access the data at any time.
- Every 6 months for 3 years, a separate “evaluation physician” (not the outpatient physician) checks the arrhythmia event data from the ILR. The results are recorded in the CRF.
- If the ILR records an arrhythmia event, an alert email is sent to the evaluation physician, who then reviews the ECG on the server to confirm. If urgent, the evaluation physician notifies the outpatient physician immediately. If the patient reports symptoms, the ILR data can be reviewed at any time.

##### 7.1.4 Outpatient Follow-up

- The patient continues outpatient visits every 1–3 months. During those visits, events related to secondary endpoints 4–8 and the subject’s clinical status are confirmed.
- Additional tests may be performed as necessary for standard care.
- No extra examinations are performed solely for this study.
- If the subject moves away, it may still be possible to continue in the study if certain conditions are met (e.g., medical records can be obtained from a local hospital, the subject agrees to return for ILR explantation unless physically impossible, etc.).

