**Protocol Treatment**
After obtaining written informed consent, the ILR will be implanted subcutaneously in the left anterior chest area under local anesthesia by the principal or sub-investigator. Post-implantation, remote monitoring (using Medtronic CareLink) will be performed every 6 months to assess the arrhythmic events specified in Section 5.1.

For the primary endpoint and secondary endpoints 1–3, if an arrhythmic event is detected via remote monitoring, an alert email will be sent or forwarded to an evaluation physician who is separate from the outpatient attending physician. The evaluation physician will review the ECG stored on the server and make a diagnosis (determine whether an arrhythmic event occurred). If the physician judges that immediate communication with the outpatient physician is medically necessary, the monitoring results will be reported to the outpatient physician as needed. If the patient experiences symptoms suggestive of arrhythmia, the ILR data may be checked at any time.

Patients will continue outpatient visits every 1–3 months, as before ILR implantation. During these visits, the presence or absence of events related to secondary endpoints 4–8 will be verified, along with other clinical progress.

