### **3. Background of the Clinical Research**

In Japan’s statistics of causes of death, heart disease ranks second; among these, heart failure accounts for the largest proportion. With an aging society, the number of heart failure patients continues to increase, projected to reach 1.2 million by 2020. About half of these patients have reduced left ventricular ejection fraction, and the 2017 revised “Guidelines for Diagnosis and Treatment of Acute and Chronic Heart Failure” define HFrEF (Heart Failure with reduced Ejection Fraction) as an LVEF <40%.

Atrial fibrillation (AF) is the most frequently coexisting arrhythmia in heart failure, and its prevalence increases in more severe heart failure cases, serving as a trigger for both exacerbation of heart failure and thromboembolism. If detected at an early stage, ablation or antiarrhythmic drug therapy can be used for rhythm control; in chronic cases, the arrhythmia may be managed by rate control with medication. Ventricular arrhythmias are also common in HFrEF and can lead to sudden cardiac death. High-risk cases may require antiarrhythmic drug therapy or implantation of an implantable cardioverter defibrillator (ICD).

Since arrhythmias typically occur intermittently and often without symptoms, diagnosing them in regular outpatient care can be difficult. It is known that the diagnostic accuracy for arrhythmias depends on the length of time ECG is evaluated (monitoring period), and implantable loop recorders (ILRs)—implanted subcutaneously in the left anterior chest—allow continuous ECG monitoring and thus provide the highest accuracy. The “Medtronic LINQ II” device we will use in this study is small and light (45 × 8 × 4.2 mm, 4 g), and its monitoring data can be checked by healthcare providers at any time via a remote monitoring system. While it is an already-approved device in Japan, domestic approval is limited to (1) patients with unexplained syncope and (2) patients with unexplained cerebral infarction. By contrast, it has broader indications in the U.S. and Europe, including use for AF monitoring. For instance, a large clinical trial by Sanna et al., involving 441 patients with cryptogenic stroke in whom AF was not detected by conventional means, randomized them into ILR implantation vs. conventional monitoring groups for 6 months, demonstrating a significantly higher detection rate of AF in the ILR group (8.9% vs. 1.4%).

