#### 7.2 Observation/Examination Items and Schedule

##### 7.2.1 Schedule

| **Observation Items** | **Pre-Implant** | **At Implant** | **Remote Monitoring After Implant** |
| --- | --- | --- | --- |
| Informed Consent (IC) | ● |  |  |
| Registration | ● |  |  |
| Subject Background Info | ● |  |  |
| ILR Implantation |  | ● |  |
| Remote Monitoring: arrhythmia events¹ |  |  | 6/12/18/24/30/36 months ±4 weeks |
| 12-lead ECG² | ● | ● |  |
| Echo (LAD, LVDd, LVDs, LVEF, etc.) | ● |  |  |
| Blood test (BNP) | ● |  |  |
| Chest X-ray | ● |  |  |
| Clinical course (every 1–3 months) |  |  | (Ongoing in standard outpatient care) |
| Adverse events, device malfunctions | (Monitored throughout the study) |  |  |

¹ ILR data are evaluated at 6-month intervals (±4 weeks).
² Baseline ECG: can be a monitor ECG at implant.

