##### 8.1.2 Secondary Endpoints

1. Proportion of patients with pauses ≥4.5 s
2. Proportion of patients with bradycardia <30 bpm
3. Proportion of patients with high-grade AV block
4. Proportion of patients receiving pacemaker, ICD, ablation, or antiarrhythmic therapy
5. All-cause mortality
6. Cardiovascular mortality
7. Proportion with hospitalizations for CV disease/HF
8. Proportion who experienced stroke

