**10.3 Handling of Cases**

- Subjects who withdraw before ILR implantation will be excluded from analysis.
- Subjects lost to follow-up will be included in the last-observation-carried-forward (LOCF) analysis.

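### The outpatient visit is the only occasion named for confirming deaths, and LOCF does not exempt mortality, so an unrecognised death can be counted as a survivor

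*Protocol*

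**What the plan says.** Section 8.1.2 lists "All-cause mortality" as secondary endpoint 5 and "Cardiovascular mortality" as secondary endpoint 6. Three places say when endpoints 4 to 8 are established, and all point to routine clinic attendance every 1 to 3 months:

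- Section 7.1.4: "During those visits, events related to secondary endpoints 4–8 and the subject’s clinical status are confirmed".
- Section 1, Protocol Treatment: "During these visits, the presence or absence of events related to secondary endpoints 4–8 will be verified, along with other clinical progress".
- Section 7.2.1, clinical course row: "Ongoing in standard outpatient care".

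Section 7.2.2 item 6 fixes what is recorded about a death, "Mortality (date, CV or non-CV, details", but names no source for it. The six-monthly remote evaluation in section 7.1.3 covers arrhythmia data.

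For subjects who drop out of sight, section 10.3 says: "Subjects lost to follow-up will be included in the last-observation-carried-forward (LOCF) analysis". No endpoint is named or exempted. Section 10.5 lists Kaplan-Meier curves for the time-to-event analyses of the secondary endpoints.

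**The concern.** A subject who has died does not attend the next visit. If nobody informs the hospital, the visit confirms nothing, and the protocol does not say that anyone must then find out whether the subject is alive. If that subject is treated as lost to follow-up, the rule in 10.3 carries the last known status forward, and the last known status is alive.

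Two of the eight secondary endpoints are affected directly. Section 5.1 says that endpoints 5 to 8 serve to relate loop-recorder findings to clinical outcomes, so an undercount of deaths weakens the data for that purpose. The gap lies in data collection, which the protocol itself fixes. An analysis plan cannot recover a death that was never recorded.

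**Working it through.** **Ascertainment.** These are the routes by which the protocol could learn of a death:

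| Route | Section | Does it establish vital status in a non-attender? |
|---|---|---|
| Outpatient visit | 1, 7.1.4, 7.2.1 | No; it needs attendance |
| Adverse event monitoring, 24-hour serious event reports | 7.2.1, 9.2, 9.4 | Only once the site has heard of the event |
| Loop-recorder alert | 1, 7.1.3 | No; it signals an arrhythmia |
| Local-hospital records | 7.1.4 | Mentioned for subjects who move away |
| Follow-up after discontinuation | 7.6, 11 | Applies once discontinuation has been recognised |

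Several routes could reveal a death. None is triggered by a missed visit, and none requires vital status to be determined.

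**Analysis rule.** Section 10.3 carries the last observation forward, so the subject stays in the denominator as a survivor. Under the Kaplan-Meier method of 10.5 the same subject would be censored. Section 10.5 does not name the endpoints to which the curves apply, but mortality is the obvious one, and the protocol does not say which rule prevails.

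**Size.** The protocol gives no expected mortality, no loss rate and no prospective sample-size calculation, so there is no figure to reproduce. The one input is N = 35 (section 10.2). With *D* true deaths and *m* of them missed and counted as alive:

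reported proportion = (*D* − *m*)/35; understatement = *m*/35; for *m* = 1, 1/35 = 2.9 points.

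For illustration only, with assumed values of *D* and *m*:

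| Assumed true deaths | True | 1 missed | 2 missed | 3 missed |
|---|---|---|---|---|
| 3 | 8.6% | 5.7% | 2.9% | 0.0% |
| 5 | 14.3% | 11.4% | 8.6% | 5.7% |
| 7 | 20.0% | 17.1% | 14.3% | 11.4% |

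With 5 deaths all captured, 5/35 = 14.3% (exact 95% CI 4.8 to 30.3). With 2 of them carried forward as alive, 3/35 = 8.6% (1.8 to 23.1).

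**Does censoring alone repair this?** Take 5 deaths, censor the second and fourth at the time of death, and assume no other censoring:

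1 − (34/35)(32/33)(30/31) = 8.8%.

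That is almost the same as the 8.6% under carry-forward and well below the true 14.3%. The pattern is the same for 3 deaths with 1 missed (5.8% against a true 8.6%) and 7 deaths with 2 missed (14.9% against 20.0%). Changing the analysis rule without finding the deaths recovers almost nothing.

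**Chance of missing at least one.** If each of 5 deaths independently has an assumed 10%, 20% or 30% chance of being missed, the chance is 1 − (1 − *q*)^5 = 41%, 67% or 83%.

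**The case against.** The strongest reply is that the protocol never says deaths are found only at visits. It says when events are confirmed and does not limit where the information comes from. Section 7.2.2 asks for the date and class of death, which cannot come from the deceased's own attendance, so outside information is presupposed. Adverse events are monitored throughout the study. Serious events are reported within 24 hours, and the definition in 9.1, although it does not name death, is not worded as exhaustive. Sections 7.6 and 11 call for discontinuation and later follow-up to be documented. Section 7.1.5 has the device explanted when follow-up fails, which presupposes contact. With visits every 1 to 3 months, an absence would soon be noticed.

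Much of this stands. A death may well become known, and it would be wrong to say that the protocol makes this impossible. But noticing an absence is not the same as establishing why. None of these provisions obliges anyone to determine vital status in a subject who simply stops coming.

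It is also fair that 10.3 does not say in so many words that mortality is carried forward, and that 10.5 points the other way. That leaves two rules in conflict, neither of which yields the right answer for an unrecognised death.

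A reader might go further and infer that deaths in subjects with ventricular tachycardia are lost selectively, since section 3 states: "Ventricular arrhythmias are also common in HFrEF and can lead to sudden cardiac death". Such a loss would pull the relation between loop-recorder findings and mortality towards no association. The documents do not support this. Every subject has continuous rhythm monitoring with alerts to an evaluation physician, so an arrhythmic death may be more likely, not less, to leave a signal. The direction of any selective loss is unknown.

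**Conclusion.** The point holds in limited form. The visit is the only occasion the protocol names for confirming all-cause and cardiovascular mortality, there is no vital-status check for a subject who stops attending, and the LOCF rule in 10.3 neither exempts mortality nor agrees with 10.5. As written, an unrecognised death can be counted as a survivor.

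The size that follows from the protocol is 2.9 percentage points per missed death, taking all 35 planned subjects as the denominator. The number missed cannot be derived; the totals above rest on assumed death counts and missed shares and are not a forecast. The bias can only be downward. It concerns two secondary endpoints of a small exploratory study whose mortality intervals will be wide in any case (25.5 points for 5 of 35: 30.3 − 4.8), and the primary endpoint is outside this point. It should still be corrected, because the repair is cheap and a missed death cannot be restored at analysis.

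**What to change.** **Data collection (7.1.4, 7.2.1 and 7.2.2 item 6).** Record vital status for every implanted subject still under observation at each scheduled loop-recorder evaluation (6, 12, 18, 24, 30 and 36 months), whether or not the subject has attended clinic. If there has been neither a visit nor a transmission since the previous check, contact the subject, the family or the local hospital for vital status and, where the subject has died, the date and cause. Only a transmission showing a recorded heart rhythm should count as evidence of life.

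**Analysis (10.3).** State that LOCF does not apply to mortality, and that subjects without a confirmed death are censored at the last-known-alive date in the Kaplan-Meier analysis, so that 10.3 and 10.5 agree.

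The two parts belong together: as the working shows, the censoring sentence does not recover a missed death by itself.

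**Cost.** One field on the case report form at six evaluations already scheduled, an occasional telephone call, and a short amendment to 10.3. No extra visit, examination or subject is needed. The downside is a little coordinator time.
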